### Intervention

In this study, we will evaluate the ACP Respecting Choices program. It involves trained healthcare professionals (“facilitators”, mostly nurses) who assist patients and their relatives in reflecting on the patient’s goals, values and beliefs and in discussing their healthcare wishes [12, 15]. The program also supports people to identify specific activities and experiences that may contribute to, or detract from, their quality of life. Patients are encouraged to appoint a patient representative who preferably also attends the Respecting Choices sessions, and to document their preferences for (future) medical treatment and care in an advance directive; the so-called My Preferences form. These wishes can e.g. concern the (non-)use of potentially burdensome life-prolonging interventions such as hospitalisations or cardio-pulmonary resuscitation. Patients are encouraged to discuss their preferences and questions they may encounter with their physician. The content of the communication during these meetings will be structured by the use of interview guides.

### Study procedures

For each participating hospital, baseline background data will be collected, such as number of cancer patients attending annually, academic/nonacademic setting, number of beds and palliative care services, and a description of common practices regarding ACP and decision-making at the end-of-life. In addition, background reports for each of the six participating countries will be created summarizing baseline national and local policies related to the provision of palliative care and ACP.

We will carefully translate the Respecting Choices program into the required European languages and adapt its content, in close collaboration with the US developers, to the specific legal, clinical, ethical, and cultural contexts of the participating European countries. To test the intervention and the process for acceptability and efficiency, a feasibility study will be conducted with five patients and potentially their family caregiver in each country. The patients will be offered the ACP program and will subsequently be interviewed. We will also test the questionnaires and have conversations with their healthcare providers.

Extensive training of the ACP facilitators is essential in this project. We will use the well-established structure of the training and implementation of the Respecting Choices program and will adopt a two-step education process. First, one representative per country will be trained in La Crosse, Wisconsin (USA) by the instructors of the Respecting Choices program. Subsequently, the country representative will train the local facilitators, who will be --where possible- selected among the healthcare workers of the hospitals, e.g. nurses. All together about 40 facilitators will be trained in the project.

Patients will be followed until one year after inclusion. During the inclusion period eligible patients in both intervention and control hospitals, will be approached for written informed consent. The information provided in the consent form for the intervention group and the control group will be as similar as possible to avoid selection bias with respect to interest in ACP. However, to minimize contamination, patients will be informed that the project aims at investigating the experiences of patients with different approaches towards medical decision-making in advanced stages of cancer, but no or limited details of the Respecting Choices program will be revealed in the control group. Patients will be given ample time to consider participation and they are free to withdraw from participating in the study without any effect on their care.

Patients in the intervention group will be offered the Respecting Choices program in addition to their usual care. Depending on the health status of the patient and the content of the conversations, a facilitated interview will last 45–60 min on average. We plan to have one or two sessions per patient. The facilitator will assist the patient in documenting preferences, including the assignment of a personal representative. For quality assurance, the interviews will be audio recorded by the facilitator.

By a standardized checklist a proportion of the interviews will be rated for intervention fidelity [16].

Ethical committee procedures have been followed in all countries and institutions involved, and approval has been provided. The names of the main IRB’s are:The Netherlands: Medische Ethische Toetsings Commissie (METC) ErasmusMC;Belgium: Universitair Ziekenhuis Brussel Commissie Medische Ethiek;United Kingdom: NRES Committee North West - Liverpool East;Italy: Comitato Etico Area Vasta Centro, Regione Toscana;Denmark: De Videnskabsetiske Komiteer for Region Hovedstaden;Slovenia: Komisija Republike Slovenije za medicinsko etiko (KME).

Approval was also obtained from the IRB’s of all the remaining institutions.

The trial is registered in the International Standard Randomised Controlled Trial Number (ISRCTN63110516). A Data Steering Monitoring Board (DSMB) will be established.

### Measurements

In ACTION, the following measurements will be performed (see Table 2):

**Table 2 Tab2:** Patient and bereaved carer endpoints of the project

I. Measured by questionnaire	Measure
*Primary endpoints:*	
- Quality of life	EORTC QLQ-C30 4-item emotional functioning scale [24]
	EORTC emotional functioning short-form based on CAT item bank
- Symptoms	EORTC QLQ-C15-PAL [25]
*Secondary endpoints:*	
- Shared decision-making	APECC [26]
- Patient involvement	Self-constructed questions
- Satisfaction with care	EORTC IN–PATSAT32 [27]
- Coping with illness	COPE [28–30]
- Satisfaction with the intervention	Self-constructed questions
- Socio demographic measures	Self-constructed questions
- Quality of end-of-life care	VOICES-SF [31]^a^
- Bereaved carer wellbeing	HADS [32]; IES [33]^a^
II. Obtained from medical files	
- Survival; date and place of death (if applicable)	
- Completion and content of advance directives; preferences for care; assignment of proxy decision-maker; physician orders	
- Diagnostic procedures and treatments received by the patient, hospitalisations and specialist palliative care input.	
III. Obtained from intervention sessions and qualitative interviews	
Systematic cross-cultural comparison of patient experiences, responses and concerns.	

^a^These endpoints are measured by the bereaved carer questionnaire and not by the patient questionnaire

Questionnaire study. Patients will be asked to complete a written questionnaire about quality of life, symptoms, the decision-making process, patient activation, coping, and satisfaction with care (and the intervention) at baseline (i.e., the moment of inclusion, before the ACP program is delivered in the intervention group), and at 2.5 and 4.5 months after inclusion. If a patient dies during follow up (i.e., within one year after inclusion), a relative identified by the patient as next of kin will receive a questionnaire to assess the patient’s quality of end-of-life care and the relative’s own wellbeing.Medical file study. Data on patients’ survival will be collected, as well as preferences as documented and care as received to assess whether patients’ preferred care was congruent with received care. Data on care as received will also be used in the cost-effectiveness analysis. These medical files will be studied one year post-inclusion with a checklist.Study of recorded ACP sessions. Data will be obtained from audio recorded facilitated interview sessions. Compliance with the intervention will be systematically evaluated with a predefined checklist.

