**Methods/Design:**

We will study the effects of the ACP program Respecting Choices on the quality of life of patients with advanced lung or colorectal cancer. In a phase III multicenter cluster randomised controlled trial, 22 hospitals in 6 countries will be randomised. In the intervention sites, patients will be offered interviews with a trained facilitator. In the control sites, patients will receive care as usual. In total, 1360 patients will be included. All participating patients will be asked to complete questionnaires at inclusion, and again after 2.5 and 4.5 months. If a patient dies within a year after inclusion, a relative will be asked to complete a questionnaire on end-of-life care. Use of medical care will be assessed by checking medical files. The primary endpoint is patients’ quality of life at 2.5 months post-inclusion. Secondary endpoints are the extent to which care as received is aligned with patients’ preferences, patients’ evaluation of decision-making processes, quality of end-of-life care and cost-effectiveness of the intervention. A complementary qualitative study will be carried out to explore the lived experience of engagement with the Respecting Choices program from the perspectives of patients, their Personal Representatives, healthcare providers and facilitators.

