Most ACP studies have been performed in the US, amongst nursing home patients with the main aim of establishing patients’ preferences before they lose their competence. We will conduct our study in a European context and hypothesize that ACP can also be effective in improving the quality of life of patients with cancer who often remain competent until death or very close to death. ACP may support them in timely recognizing and continuously expressing their core values and preferences, and to communicate these with their loved ones and professional care givers, which will enable strategic and effective planning of care and decision-making. As a result, care may more adequately address patients’ values and preferences, which may result in improved quality of life and more adequate symptom control, while patients feel more in control and receive less unwanted or futile interventions.

The overall hypothesis that will be studied in the ACTION project is that a formalized ACP program such as Respecting Choices significantly improves the quality of life and reduces the symptom burden of patients with advanced lung or colorectal cancer.

The primary objective is to assess the effect of the Respecting Choices ACP program on the quality of life and symptoms of patients with advanced lung or colorectal cancer.

The secondary objectives are:To assess the effect of the Respecting Choices ACP program on the quality of life and symptoms of patients with advanced cancer in different subgroups (gender, age, education, ethnicity, country and type of cancer).To assess the effect of the Respecting Choices ACP program on the extent to which care as received is in line with patients’ documented preferences, on patients’ evaluation of the quality of the decision-making process, and on how they cope with their illness.To assess patient satisfaction with the Respecting Choices ACP program.To assess the effect of the Respecting Choices ACP program on the quality of end of life care of patients with advanced cancer from the bereaved carers’ perspective, and on the wellbeing of these carers.To assess the cost effectiveness of the Respecting Choices ACP program.To gain insight into how patients, patients’ relatives and professional caregivers experience and respond to facilitated ACP.

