### Power calculation, sample size and feasibility of recruitment

With at least 11 intervention and 11 control hospitals each recruiting 34 lung cancer patients and 34 colorectal cancer patients (of which 25 in each tumour type group are expected to remain in the study until at least month 2.5), this multicentre cluster-randomised clinical trial has an overall power of 90 % to identify a minimum difference between intervention and control groups of half a standard deviation on the emotional functioning scale of the QLQ-C30 scale, assuming an intra-class correlation (ICC) of 0.1. On country level, these numbers give a power of 50 % to show such a difference (assuming an ICC of 0.05).

The main outcomes are measured at 2.5 months post-inclusion. Although included patients have an average life expectancy of at least 3 months, we expect that a number of them will die within 2.5 months after inclusion. Based on Dutch colorectal and lung cancer survival statistics [23], we conservatively assume that this will be the case for 15 % of included patients. Furthermore, we anticipate that around 10 % of included patients may drop out of the study for other reasons, resulting in a total attrition rate of 25 %. Based on this attrition rate and an estimated willingness of patients to participate of 33 %, the total number of eligible patients per hospital per cancer type needs to be 101 in a 2-year period, which is feasible in the participating hospitals.

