### Analyses

Analyses of the primary and secondary endpoints will be performed following the intention-to-treat principle. Descriptive statistics will be used to summarize characteristics of countries, hospitals and patients. Patient characteristics (age, gender, socio-economic class, educational level) will be compared at baseline between the intervention and control group. A multilevel modelling approach will be used to examine differences in the endpoints between the intervention and control groups, taking account of clustering effects at both hospital and country-level. All statistical tests will be two-sided and considered significant if *p* < 0.05. Repeated-measures analyses of variance will be conducted to assess the development of endpoints over time.

Subgroup analysis will be conducted by means of formal interaction tests for intervention and those variables which are more likely to influence the effect of the intervention itself: gender, age class (<65, 65–74, 75+), educational status, and country.

Those conducting the data analysis will be blinded as to whether the patient was included in the intervention group or in the control group.

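### The primary endpoint is stated inconsistently, and no section says which result decides the trial

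*Protocol article*

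**What the plan says.** The sections of the protocol article describe the primary endpoint differently.

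- **Abstract, Methods/Design:** one endpoint, in the singular: "The primary endpoint is patients’ quality of life at 2.5 months post-inclusion". No instrument is given. Symptoms are not part of it, and the abstract's list of secondary endpoints does not contain them either.
- **Background, primary objective:** two domains are covered, "on the quality of life and symptoms of patients with advanced lung or colorectal cancer". Likewise, the overall hypothesis joins better quality of life and lower symptom burden.
- **Measurements, Table 2:** a plural heading for primary endpoints. Quality of life has two measures, the QLQ-C30 4-item emotional functioning scale and the "EORTC emotional functioning short-form based on CAT item bank". Symptoms have the QLQ-C15-PAL, with no scale or item named.
- **Power calculation:** 90% power for a difference of "half a standard deviation on the emotional functioning scale of the QLQ-C30 scale". No other measure is powered. The section refers to main outcomes in the plural, whereas the Discussion refers to the main outcome measure in the singular.
- **Analyses:** "All statistical tests will be two-sided and considered significant if" p < 0.05. No order or ranking of the primary measures is given.
- **Cost-effectiveness study:** the effect in the cost-effectiveness ratio is the QLQ-C30 4-item emotional functioning scale.

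**The concern.** A confirmatory trial needs one rule, fixed in advance, that turns the results into success or failure. This article allows at least three: success on QLQ-C30 emotional functioning alone, success on any measure listed as primary in Table 2, or success on both quality of life and symptoms. These rules have different error rates and different power, and the same data could pass one and fail another.

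Suppose the QLQ-C30 scale shows no effect while the short form or a symptom score is significant. That could be reported as a positive trial in keeping with Table 2, on a measure for which the article states no power. The freedom matters more than usual here because patients and staff cannot be blinded and the outcomes are self-reported.

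**Working it through.** **1. Reproduce the stated power.** Inputs from the power section: 11 hospitals per arm (k), 25 + 25 = 50 evaluable patients per hospital (m), ICC 0.1, difference 0.5 SD. Two-sided alpha of 0.05 is from Analyses.

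- Design effect: 1 + (m − 1) × ICC = 1 + 49 × 0.1 = 5.9
- Effective sample per arm: k × m / 5.9 = 550 / 5.9 = 93.2
- Noncentrality: 0.5 / √(2 / 93.2) = 3.41
- Power: 92.7% (normal approximation), or 90.1% (noncentral t with 2k − 2 = 20 degrees of freedom)

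The stated 90% is reproduced for one test of one measure at alpha 0.05.

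**2. Reading A: any one primary measure suffices.** With K independent tests at 0.05 the family-wise error is 1 − 0.95^K:

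- K = 2 (one quality-of-life measure and one symptom measure): 1 − 0.9025 = 9.75%
- K = 3 (the three instruments of Table 2, one test each): 1 − 0.857375 = 14.3%

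The measures are not likely to be independent, and the documents give no correlations. The values below are therefore assumptions, applied equally to all pairs of test statistics (simulation of one million correlated normal draws, critical value 1.96):

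| Assumed correlation | 2 tests | 3 tests |
|---|---|---|
| 0 (exact formula) | 9.75% | 14.3% |
| 0.5 | 9.1% | 12.6% |
| 0.7 | 8.3% | 11.0% |
| 0.9 | 7.1% | 8.4% |

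With an assumed 0.9 between the two emotional functioning measures and 0.5 between each of them and symptoms, three tests give 10.9%. Every case examined is above 5%.

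If this reading were kept with a Bonferroni split, power for 0.5 SD on the QLQ-C30 scale would fall from 90.1% to 83.0% (alpha 0.025, two tests) or 78.0% (alpha 0.0167, three tests) on the t basis. On the normal basis it would fall from 92.7% to 87.9% or 84.6%.

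**3. Reading B: quality of life and symptoms must both succeed.** When each must be significant at 0.05, the chance of a false claim on both is at most 5%, so alpha is not inflated. The chance of success, however, cannot exceed the smaller of the two powers. If the tests were independent it would be 0.90 × (power for symptoms). The article gives no effect size, standard deviation or ICC for symptoms, so this cannot be computed. Purely as an illustration, a symptom power of 90% would give 0.90 × 0.90 = 81%.

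**4. Reading C: QLQ-C30 emotional functioning alone.** Error rate 5% and power 90%, as stated. Only this reading makes the sample-size statement the power for trial success, and no section says that it applies.

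**The case against.** The best defence is that the intention can be inferred. The abstract gives one endpoint and one time point, the sample size and the cost-effectiveness ratio both use the QLQ-C30 4-item scale, and the Discussion speaks of one main outcome measure. The 0.05 threshold can be read as a general convention rather than a decision rule, and testing order is commonly left to an analysis plan that is not shown here. Table 2 can also be read as two endpoints, with the short form a second measure of the first.

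Much of this stands. The absence of a multiplicity procedure is not itself the finding, and the count of three primary tests is not settled, which is why figures for two are given as well. But which endpoints are primary is not a detail left open: it is stated, and stated differently in the abstract, the objective and Table 2. An analysis plan could not agree with all of them, and no section names the QLQ-C30 scale as the sole primary measure.

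Three stronger readings are tempting and are not supported:

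- **That the trial's false-positive rate exceeds 5% outright.** This holds only if any one measure suffices, which no section says. The wording of the hypothesis leans the other way.
- **That the 90% power is wrong.** It is correct for the scale it names.
- **That each QLQ-C15-PAL scale is a further primary test, with much larger inflation.** The article does not say how many would be tested, so no figure can rest on it.

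**Conclusion.** The inconsistency between current sections is real and leaves the trial without a unique success criterion. Its cost depends on the rule. If any listed measure may carry the claim, the error rate is 9.75% (two tests) or 14.3% (three) under independence, and about 7–9% or 8–13% at assumed correlations of 0.9 to 0.5. If both domains are required, the error rate is sound but the power for success is not the stated 90% and is unknown. These are alternatives: inflation from Reading A and loss of joint power from Reading B cannot be charged together. The correlations are assumptions, and the documents give nothing from which to estimate them. This should be settled before any outcome comparison is seen.

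**What to change.** State in the abstract, primary objective, Table 2 and Analyses that the single primary endpoint is the QLQ-C30 4-item emotional functioning score at 2.5 months, tested at two-sided 0.05. List the CAT-based short form and the QLQ-C15-PAL symptoms as secondary. Align the objective and hypothesis in the Background and the aim at the start of the Discussion, all of which now include symptoms or symptom burden.

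This needs no extra patients, visits or data, and it keeps both the 5% error rate and the stated power. It is still a change of substance: symptoms leave the primary objective, and neither they nor the short form can carry a primary claim.

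If symptoms are to stay primary, name the QLQ-C15-PAL scale and time point and state the success rule: either endpoint suffices, with an alpha adjustment, or both are required. Then restate the power for that rule. For the first option with alpha split over two tests, power for 0.5 SD on the QLQ-C30 scale is 83.0% on the t basis. The second needs an effect size, standard deviation and ICC for symptoms, which the article does not give.

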### Data management

Our data collection tool GemsTracker will be used to safely store data of all participating patients across hospitals and countries. GemsTracker enables restricted access to selected parts of its content. Legislation in the participating countries for research on humans, not involving medical products, will be taken into account [17–22].

### Power calculation, sample size and feasibility of recruitment

With at least 11 intervention and 11 control hospitals each recruiting 34 lung cancer patients and 34 colorectal cancer patients (of which 25 in each tumour type group are expected to remain in the study until at least month 2.5), this multicentre cluster-randomised clinical trial has an overall power of 90 % to identify a minimum difference between intervention and control groups of half a standard deviation on the emotional functioning scale of the QLQ-C30 scale, assuming an intra-class correlation (ICC) of 0.1. On country level, these numbers give a power of 50 % to show such a difference (assuming an ICC of 0.05).

The main outcomes are measured at 2.5 months post-inclusion. Although included patients have an average life expectancy of at least 3 months, we expect that a number of them will die within 2.5 months after inclusion. Based on Dutch colorectal and lung cancer survival statistics [23], we conservatively assume that this will be the case for 15 % of included patients. Furthermore, we anticipate that around 10 % of included patients may drop out of the study for other reasons, resulting in a total attrition rate of 25 %. Based on this attrition rate and an estimated willingness of patients to participate of 33 %, the total number of eligible patients per hospital per cancer type needs to be 101 in a 2-year period, which is feasible in the participating hospitals.

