## Methods/design

### Study design and setting

We will perform a multicenter cluster-randomised clinical trial in 22 hospitals in six European countries (Belgium, Denmark, Italy, the Netherlands, Slovenia and the United Kingdom). Per country pairs of comparable hospitals (academic/non-academic) will be randomised to provide either ‘care as usual’ supplemented with ACP or ‘care as usual’. Cluster-randomisation prevents healthcare providers from giving patients in the control group (‘care as usual’) more opportunity to discuss their preferences than usual due to their experience with providing the intervention in the intervention group (‘care as usual’ supplemented with ACP). The nature of the intervention makes blinding, for both healthcare professionals and patients and their relatives, impossible.

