### Study population

In total, 1,360 patients with advanced lung (*N* = 680) or colorectal cancer (*N* = 680) will be included. Lung and colorectal cancer patients are selected for this study because both types of cancer have high incidence and mortality rates in Europe and affect both sexes; see Table 1 for in- and exclusion criteria. At inclusion, the average life expectancy of these patients is about one year; their minimum estimated life expectancy to be eligible for the study is three months.

**Table 1 Tab1:** Inclusion and exclusion criteria

Inclusion criteria	Exclusion criteria
Histologically confirmed diagnosis of: • Lung cancer:	Age < 18 years
- small cell - extensive disease/Stage III or IV* - non-small cell - stage III or IV*	Unable to provide consent
• Colorectal cancer: Stage IV or metachronous metastases*	Unable to complete questionnaire in country’s language
*according to 7th edition of TNM classification and staging system	Less than 3 months anticipated life expectancy
Written informed consent to participate	Taking part in a research study that is evaluating palliative care services or communication strategies.
WHO performance status of 0–3.	

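### The declared total of 1,360 patients does not equal the design behind the stated power, which multiplies out to at least 1,496

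*Protocol article*

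**What the plan says.** All references are to the protocol article.

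- **Abstract, Methods/Design:** "22 hospitals in 6 countries will be randomised", and "In total, 1360 patients will be included".
- **Study design and setting:** "We will perform a multicenter cluster-randomised clinical trial in 22 hospitals in six European countries".
- **Study population:** "In total, 1,360 patients with advanced lung"; colorectal cancer is the second tumour type, and the split is 680 and 680.
- **Power calculation, sample size and feasibility of recruitment:** the design is set out as "With at least 11 intervention and 11 control hospitals each recruiting 34 lung cancer patients and 34 colorectal cancer patients". After losses, 25 + 25 patients per hospital should still be available at 2.5 months. For this design the article claims 90% power at an ICC (intra-class correlation) of 0.1, and it fixes the target difference at "half a standard deviation on the emotional functioning scale". The same numbers are said to give 50% power within a country at an ICC of 0.05. Attrition is put at 25% and willingness to participate at 33%, which leads to 101 eligible patients needed per hospital per cancer type.

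**The concern.** The planned sample size should follow from the inputs of the power calculation. Here the hospitals and the per-hospital recruitment in the power section give a larger total than the one declared in the abstract and the Study population section. If 1,360 is right, 22 hospitals cannot each recruit 34 + 34, so the 25 + 25 evaluable patients per hospital used for the power are not what the trial will have. If 34 + 34 is right, the trial will enrol at least 136 more patients than it declares. The final report will have to compare actual with planned recruitment, and any shortfall would depend on which section is cited.

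**Working it through.** **Inputs from the article.** 22 hospitals, at least 11 per arm; 34 + 34 = 68 recruited per hospital; 25 + 25 = 50 evaluable per hospital at 2.5 months; difference 0.5 SD; ICC 0.1; two-sided 5% level (Analyses section); attrition 25%; willingness 33%.

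**1. Total.**
- 22 × 68 = 1,496, and 22 × 34 = 748 per tumour type. Because the text says at least 11 per arm, this is a minimum.
- 1,496 − 1,360 = 136, and 136 / 1,360 = 10.0%.

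**2. Do attrition or rounding explain the gap?**
- Evaluable patients: 22 × 50 = 1,100, so 1,360 is not an after-attrition count.
- Inflating for attrition: 1,100 / 0.75 = 1,467, which also misses 1,360.
- 1,360 / 68 = 20 exactly, and 680 / 34 = 20 exactly.
- 1,360 / 22 = 61.8 per hospital, or 30.9 per tumour type.
- Eligible patients: 25 / 0.75 = 33.3 recruits and 33.3 / 0.33 = 101. The feasibility figure therefore belongs with 25 evaluable per tumour type, not with 30.9 recruited.

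**3. The stated power.** The article does not name its power method, so two are shown. With k hospitals per arm and m evaluable per hospital:
- design effect = 1 + (m − 1) × ICC
- effective n per arm = k × m / design effect
- noncentrality = 0.5 × √(effective n / 2)

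Power is then read from the normal distribution or from a noncentral t with 2k − 2 degrees of freedom.

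For k = 11 and m = 50, the design effect is 1 + 49 × 0.1 = 5.9. The effective n is 550 / 5.9 = 93.2, and the noncentrality is 0.5 × √46.6 = 3.41. Power is 90.1% (t, 20 df) or 92.7% (normal). The t version reproduces the stated 90%.

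**4. Power if 1,360 patients are spread over 22 hospitals.** Evaluable per hospital: 61.8 × 0.75 = 46.4. The design effect is 5.54, the effective n is 92.1 and the noncentrality is 3.39.

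| Design | Patients enrolled | Evaluable per hospital | Power, t | Power, normal |
|---|---|---|---|---|
| 22 hospitals, 34 + 34 | 1,496 | 50 | 90.1% | 92.7% |
| 22 hospitals, declared total | 1,360 | 46.4 | 89.7% | 92.4% |

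Using the article's own retention of 25 out of 34 instead of 75% gives 45.5 evaluable per hospital, and 89.6% or 92.3%. At an ICC of 0.1 the number of hospitals drives the power. Losing four or five evaluable patients per hospital costs about half a percentage point or less.

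**The case against.** The best case against raising this is that it changes nothing of substance. The estimand, the analysis and the effect size are untouched, and power for 1,360 patients over 22 hospitals still rounds to 90% by the t-test and exceeds it by the normal approximation. Only one total is ever declared: 1,360 appears in both the abstract and the Study population section, while 1,496 appears nowhere and is a product of planning inputs. Recruitment-closure rules and site quotas belong in the full protocol, which is not shown. All of this stands, and it limits the weight of the point. It does not remove the point, because the article states both sets of figures and they conflict. Condensing a longer document does not account for that.

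A reader might infer three stronger things.

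- **That the trial is underpowered.** The calculation shows otherwise.
- **That 1,360 was carried over from a 20-hospital design.** The exact match with 20 × 68 makes this plausible, but no section mentions 20 hospitals, so it remains inference. For the same reason, the power of a 20-hospital trial (86.8% by t, 90.2% by the normal approximation) should not be counted as a consequence.
- **That sites cannot know when recruitment is complete.** With a single declared total, and the operational rules not shown, the article does not support this.

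**Conclusion.** The inconsistency is real. The declared 1,360 falls 136 short of the minimum of 1,496 implied by the power section, a 10% gap that neither attrition nor rounding explains. Its effect on power is about half a percentage point or less if all 22 hospitals recruit. This rests on the article's own ICC of 0.1 and 25% attrition, and on two assumptions of this check: hospitals of equal size and a simple two-arm comparison of cluster means. It is a consistency error in the planned sample size that should be corrected, not a flaw that puts the primary analysis at risk.

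**What to change.** Bring the abstract, the Study population section and the power section to one set of figures. The choice is the sponsor's.

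**(a) Keep 22 hospitals and about 1,360 patients.**
- Restate the per-hospital figure as about 31 + 31 enrolled. At 25% attrition this is 31 × 0.75 = 23.25, so about 23 + 23 evaluable.
- The total becomes 22 × 62 = 1,364 (682 per tumour type), so 1,360 and 680 + 680 must be changed or described as approximate.
- State power as about 90% (89.7% by t).
- Eligible patients needed become 31 / 0.33 = about 94 per hospital per tumour type instead of 101.
- Re-check the country-level power, because the article ties it to the same numbers.

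**(b) Keep 34 + 34 per hospital.** Restate the planned total as 1,496 (748 per tumour type) in the abstract and the Study population section. The power section can stay as it is.

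Either way the change is to wording only. Option (a) adds four patients to the declared total and moves the stated power by less than one percentage point. Option (b) adds 136 to the declared total.
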